### Data Management and Quality Control

Data will be primarily collected using paper-based CRFs. To ensure data quality and accuracy, all data from the CRFs will be independently entered into a designated electronic database by 2 researchers. This process of double data entry and cross-verification will help minimize input errors. In case of inconsistent entries or identified omissions, the original CRFs will be rechecked for clarification and correction. To protect participant confidentiality, all personal identifiers will be removed and replaced with unique coded identification numbers in all electronic databases and analysis reports. The original paper CRFs will be securely stored in locked file cabinets at the principal investigator’s institution. The electronic database will be stored on a password-protected computer, with access restricted to authorized research personnel only. Participant personal information will not be disclosed under any circumstances without their written consent. After the database is locked, no further alterations will be permitted.

### Ethical Considerations

This study was approved by the Medical Ethics Committee of the Hunan Academy of Traditional Chinese Medicine Affiliated Hospital ({2025}29). This study will be conducted in accordance with the ethical principles of the Declaration of Helsinki. Informed consent will be obtained from all participants or their legal guardians before their enrollment in the study (informed consent is displayed in Multimedia Appendix 2). To protect participant privacy, all personal identifiers will be removed and replaced with a unique code; the list linking codes to identities will be stored separately under strict security measures.

## Results

This study was funded by the National Natural Science Foundation of China General Program (grant 8237153821). Participant recruitment commenced in April 2025 across the 4 participating centers and is projected to be completed by December 2026. Final data collection, including all 12-week follow-up assessments, is anticipated to conclude by April 2027. As of November 2025, a total of 47 participants have been enrolled, 28 of whom have completed the follow-up assessments. Data analysis will commence following the completion of data collection. The primary results of this study are expected to be submitted for publication in September 2027.

## Discussion

### Rationale and Context

VCI is a recently recognized clinical entity primarily caused by cerebrovascular diseases [32,33]. Diverse etiologies contribute to VCI, including CSVD, large artery atherosclerosis, intracerebral hemorrhage, cardioembolism, and other less common stroke mechanisms [34,35]. VCI encompasses a spectrum of cognitive deficits, ranging from mild cognitive impairment to VaD, which arises from ischemic or hemorrhagic vascular pathologies either independently or synergistically with neurodegenerative processes such as Alzheimer disease [36]. Epidemiological projections estimate that the global burden of VCI will escalate to 100 million cases by 2050, incurring economic losses approaching US $4 trillion [37]. Although the current prevalence of VCI remains relatively low in low- and middle-income countries undergoing early demographic transitions, the most rapid growth rates in incidence are occurring there, suggesting a significant future disease burden [38]. CSVD represents a critical subtype of VCI and is the most prevalent etiological contributor to VaD in clinical practice [39]. Despite the high incidence and substantial societal burden of CSVD-related cognitive impairment, targeted therapeutic research remains scarce. Current interventions predominantly focus on VaD populations, with limited studies addressing subcortical VCI. However, TCM has long been associated with dementia treatment, supported by extensive research on TCM-based interventions [40]. TCM offers distinct advantages, including fewer adverse effects, cost-effectiveness, suitability for long-term use, and preventive potential [41], positioning it as a significant complementary and alternative therapeutic option for CSVD-related cognitive dysfunction.

The zishenyizhi pill, an empirical formula rooted in TCM theory, targets the core pathogenesis of CSVD by addressing yin deficiency and blood stasis. Preliminary clinical observations suggest its safety and efficacy in managing CSVD-related cognitive impairment; however, there is a lack of robust evidence from high-quality studies. To rigorously evaluate the zishenyizhi pill’s therapeutic impact, this study uses the MoCA as the primary end point due to its superior sensitivity and specificity in detecting cognitive deficits compared to the MMSE. Secondary outcomes will assess multidimensional cognitive domains and functional efficacy through validated neuropsychological scales.

### Limitations

Nevertheless, this study is subject to several methodological limitations. The nonrandomized observational design carries an inherent risk of selection bias and confounding. Despite stratification based on zishenyizhi pill use, baseline differences in patient characteristics—such as disease severity, comorbidities, and socioeconomic status—may persist between the intervention and control groups, potentially influencing outcome interpretation. The absence of randomization compromises internal validity as unmeasured confounders, including genetic predispositions and lifestyle factors, could independently affect cognitive trajectories.

Although real-world studies prioritize external validity, the limited control over confounding variables constrains the ability to establish causal inferences regarding the therapeutic efficacy of zishenyizhi. In addition, the sample size, while feasible for this preliminary investigation, was not derived from a formal superiority test calculation and was based on a conservative effect size estimate. Consequently, this study may be underpowered to detect differences smaller than 0.5 points on the MoCA, which could represent clinically meaningful but more modest treatment effects, particularly for secondary outcomes. This also limits the potential for meaningful subgroup analyses to explore personalized treatment responses.

Furthermore, the reliance on neuropsychological scales as primary end points without incorporating neuroimaging biomarkers such as magnetic resonance imaging–based quantification of white matter hyperintensity volume or microbleed burden restricts mechanistic interpretation. Objective biomarkers are essential to determine whether cognitive improvements correspond to structural or molecular changes in CSVD pathology. Finally, the 12-week observation period may be insufficient to evaluate the long-term efficacy, safety, and sustained cognitive benefits of zishenyizhi given the chronic and progressive nature of CSVD. Short-term assessment could miss delayed treatment effects, disease progression patterns, or late-emerging adverse events, which are critical in the context of vascular cognitive disorders.

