### Sample Size

The primary objective of this trial was to evaluate the therapeutic efficacy of zishenyizhi pill in patients with CSVD-related cognitive impairment. The sample size was estimated based on an anticipated superiority in the MoCA score among the intervention group compared to the control group. On the basis of previous pilot data and clinical judgment, we assumed a mean difference (δ) in MoCA score change of 0.5 between the 2 groups, with a common SD (σ) of 1.52. A 2–independent-sample *t* test was used for the calculation. With a significance level (α; 2-sided) set at .05, a desired power (1 – β) of 90% for detecting this difference, and an allocation ratio (*K*) of 1:1, the required sample size per group was calculated using the following formula for a superiority trial: 
[figure not shown]

. As a result, 98 participants were needed in the experimental and control groups. Accounting for a 20% anticipated dropout rate, we planned to enroll 123 participants per group, totaling 246.

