### Future Directions

Despite these constraints, this study represents a pivotal step in bridging TCM paradigms with modern clinical research methodologies. The limitations identified herein provide a clear road map for future research. To definitively establish the efficacy of zishenyizhi, subsequent studies should prioritize a multicenter RCT design to overcome the selection bias inherent in this observational approach. This RCT should be explicitly powered for superiority testing, with a sample size calculated based on a formally justified effect size for a prespecified primary cognitive end point. To elucidate the neurobiological mechanisms and move beyond reliance on neuropsychological scales alone, future trials should incorporate multimodal neuroimaging and fluid biomarkers. Furthermore, given the chronic progression of CSVD, extended intervention and follow-up periods are essential to evaluate the long-term sustainability of cognitive benefits and the intervention’s impact on disease progression. Finally, leveraging larger cohorts will enable subtype stratification based on clinical, imaging, or biomarker profiles to identify patient subgroups most likely to benefit from zishenyizhi, thereby advancing toward personalized medicine in CSVD. These concerted efforts will be crucial in robustly validating this TCM intervention and advancing its integration into global therapeutic strategies for CSVD.

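### Sample Size and Limitations give incompatible origins for the same 98 per group, and neither is right: power at the 0.5-point design difference is about 63% to 73%, not 90%.

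*Protocol article*

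**What the plan says.** **Sample Size (Methods).** The size rests on a superiority hypothesis: "The sample size was estimated based on an anticipated superiority in the MoCA score among the intervention group compared to the control group". The assumed difference is "in MoCA score change of 0.5 between the 2 groups", attributed to pilot data and clinical judgment, with a common SD of 1.52. The other inputs are a two-independent-sample t test, two-sided alpha .05, 90% power and 1:1 allocation. The article then states that "the required sample size per group was calculated using the following formula for a superiority trial". The formula itself is a figure that is not shown. The result is 98 per group, raised to 123 per group (246 in total) for 20% dropout.

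**Limitations (Discussion).** Here the sample size is said to be feasible for a preliminary investigation, but it "was not derived from a formal superiority test calculation and was based on a conservative effect size estimate". The study is said, as a consequence, to be possibly "underpowered to detect differences smaller than 0.5 points on the MoCA, which could represent clinically meaningful but more modest treatment effects".

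**Future Directions (Discussion).** Of a later trial the article says "This RCT should be explicitly powered for superiority testing", with a formally justified effect size.

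**Statistical Analysis (Methods).** The primary test is an analysis of covariance (ANCOVA) on the MoCA change at 12 weeks, adjusted for baseline MoCA, two-tailed, with P<.05.

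**The concern.** One section describes a complete superiority calculation, and another denies that the sample size came from one. Both statements are in the current text, and nothing elsewhere in the article reconciles them.

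Limitations also does not hold together by itself. A conservative design effect is a small one; it gives a larger sample and protects power. Yet the text moves from a conservative effect size to a study that may be underpowered. Nothing in Sample Size supports the word, since it cites only pilot data and clinical judgment.

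What is at stake is how the primary result will be read. Someone relying on Sample Size would take a nonsignificant MoCA comparison as the outcome of a test with a 10% chance of missing a true 0.5-point difference. Someone relying on Limitations would suppose that power is adequate at 0.5 and falls short only below it. If the planned number does not deliver 90% power at 0.5, both readers are misled.

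**Working it through.** **Inputs, all from Sample Size:** difference d = 0.5; SD s = 1.52; two-sided alpha .05 (z = 1.960); 90% power (z = 1.282); 1:1 allocation; 98 evaluable and 123 enrolled per group.

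**1. Trying to reproduce 98.** The two-sample formula is n per group = 2 × [s(1.960 + 1.282)/d]².
- (1.52/0.5)² = 9.2416, and (3.242)² = 10.51; the product is 97.1.
- With the factor 2 for two groups: 2 × 97.1 = 194.2, so **195 per group** (196 by the exact noncentral t).
- Without the factor 2: 97.1, rounded up to **98**, the stated figure.

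Other settings with the same difference and SD do not give 98: two-sided with 80% power needs 146 per group, one-sided .05 with 90% power needs 159, and one-sided .05 with 80% power needs 115. Omission of the factor 2 is therefore the likely source. This is inferred from the arithmetic, because the formula is not visible.

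**2. Dropout step.** 98/0.8 = 122.5, so 123. This step is correct. From 195 it would be 195/0.8 = 243.75, so 244 per group or 488 in total.

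**3. Power delivered at 0.5.** SE = 1.52 × √(2/n).

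| Analysed per group | SE | 0.5/SE − 1.960 | Power at 0.5 | Difference detectable with 90% power (3.242 × SE) | 95% CI half-width (1.960 × SE) |
|---|---|---|---|---|---|
| 98 | 0.217 | 0.343 | 63% | 0.70 | 0.43 |
| 123 | 0.194 | 0.620 | 73% | 0.63 | 0.38 |

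The exact t calculation gives 63% and 73% as well.

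**4. Possible gain from baseline adjustment.** If r is the correlation between baseline MoCA and MoCA change, the SD becomes 1.52 × √(1 − r²). The number per group for 90% power is then 177 at r = 0.3, 146 at r = 0.5, 125 at r = 0.6 and 100 at r = 0.7. The planned 98 would suffice only with r of about 0.7. The article states no value of r, and Sample Size bases its calculation on the unadjusted t test.

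**5. The two accounts against the result.** Sample Size claims 90% power at 0.5; its own inputs give 63% to 73%. Limitations denies a superiority calculation, although 98 follows from the listed superiority inputs once the factor 2 is dropped. It also places the shortfall only below 0.5, when the shortfall is already present at 0.5.

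**The case against.** Much of the Limitations wording is ordinary. Any study has less power below its design difference, and saying that smaller effects could matter contradicts nothing: Sample Size never presents 0.5 as a minimal important difference. Future Directions alone is also compatible with a present calculation based on pilot data and judgment. And the caution in Limitations points in the right direction, because the study is underpowered. All of this stands. It means that deleting the denial and leaving Sample Size as the only account would make matters worse, since a 90% claim that the inputs do not support would remain unqualified.

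A reader might infer more: that the two accounts let the authors claim a positive result under the superiority design and explain away a negative one as preliminary. The article does not support this. Statistical Analysis fixes the outcome, the model, two-tailed testing and P<.05. Limitations and Conclusions already restrict causal claims because the design is nonrandomized. The power caveat is confined to differences below 0.5 and aimed particularly at secondary outcomes; nowhere does the article say that a null result will be set aside. With a half-width of about 0.43, many nonsignificant results would indeed be inconclusive.

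It can also be said that a formal rule for reading the primary result commonly belongs in a statistical analysis plan, which is not shown. That is fair, and the absence of such a rule is not part of this point.

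None of this removes the contradiction over where the sample size came from, or the error in the stated power.

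**Conclusion.** The point holds as an inconsistency between Sample Size and Limitations in which both accounts are wrong as printed. The stated inputs need about 195 evaluable participants per group, roughly twice the 98 given. The planned study has about 63% power at 0.5 with 98 analysed per group, and about 73% if all 123 are analysed without loss. Limitations understates the shortfall by placing it only below 0.5, and its use of *conservative* is unsupported.

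These figures assume that the SD of 1.52 applies to the MoCA change, that the groups are equal, and that there is no gain from baseline adjustment. Adjustment could raise the power, but 90% with 98 per group would need a baseline-to-change correlation of about 0.7, for which the article gives no basis. The contradiction does not depend on any of these assumptions.

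**What to change.** Replace the two accounts with one, and keep enrolment at 246.

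- **Sample Size:** replace the 90% power claim with the power actually delivered at 0.5 (about 63% with 98 per group, about 73% with 123), or with the difference detectable with 90% power (about 0.70 with 98 per group). If the sponsor relies on a gain from baseline adjustment, state the assumed correlation and its source.
- **Limitations:** delete the statement that the size was not derived from a superiority calculation, and delete the word *conservative*. State that the study is underpowered at 0.5 points itself, not only below it. This must be done together with the Sample Size correction, not instead of it.
- **Statistical Analysis:** report the adjusted primary MoCA difference with its 95% confidence interval, so that a nonsignificant result is read from the interval. A formal three-way decision rule is optional.

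The cost is wording in three sections and a less favourable stated power. No patients or data are affected. Results puts enrolment at 47 as of November 2025, with data analysis to begin after data collection ends, so the correction can be made before the outcomes are analysed.

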### Future Directions

Despite these constraints, this study represents a pivotal step in bridging TCM paradigms with modern clinical research methodologies. The limitations identified herein provide a clear road map for future research. To definitively establish the efficacy of zishenyizhi, subsequent studies should prioritize a multicenter RCT design to overcome the selection bias inherent in this observational approach. This RCT should be explicitly powered for superiority testing, with a sample size calculated based on a formally justified effect size for a prespecified primary cognitive end point. To elucidate the neurobiological mechanisms and move beyond reliance on neuropsychological scales alone, future trials should incorporate multimodal neuroimaging and fluid biomarkers. Furthermore, given the chronic progression of CSVD, extended intervention and follow-up periods are essential to evaluate the long-term sustainability of cognitive benefits and the intervention’s impact on disease progression. Finally, leveraging larger cohorts will enable subtype stratification based on clinical, imaging, or biomarker profiles to identify patient subgroups most likely to benefit from zishenyizhi, thereby advancing toward personalized medicine in CSVD. These concerted efforts will be crucial in robustly validating this TCM intervention and advancing its integration into global therapeutic strategies for CSVD.

### Conclusions

This ongoing multicenter real-world study represents a critical effort to evaluate the integrative use of zishenyizhi pill with conventional therapy for cognitive impairment in CSVD. By combining TCM principles with modern clinical methodologies, this trial aims to address the unmet need for targeted therapies in CSVD-related cognitive decline. While the nonrandomized design and reliance on neuropsychological end points may limit causal inferences, this study’s pragmatic approach provides valuable insights into TCM’s applicability in real-world settings. Pending completion, the findings will lay the groundwork for future randomized trials to validate efficacy, elucidate mechanisms (eg, through neuroimaging biomarkers), and optimize personalized treatment strategies. This protocol highlights the potential of TCM as a complementary paradigm in global dementia research, bridging traditional knowledge with evidence-based practice.

## Appendix

Multimedia Appendix 1 Dementia Syndrome Differentiation and Classification Scale.

Multimedia Appendix 2 Informed consent form.

## Abbreviations

CRF: case report form
CSVD: cerebral small vessel disease
MMSE: Mini-Mental State Examination
MoCA: Montreal Cognitive Assessment
RCT: randomized controlled trial
TCM: traditional Chinese medicine
TMT-A: Trail Making Test part A
TMT-B: Trail Making Test part B
VaD: vascular dementia
VaDAS-cog: Vascular Dementia Assessment Scale cognitive subscale
VCI: vascular cognitive impairment
